## 2. Materials and Methods

### 2.1. Study Design

This is a cross-sectional, vignette-based experiment with a four-level within-subjects (repeated-measures) design. Vignette experiments combine the internal validity of experimental manipulation with survey feasibility and are an established method for isolating drivers of health-related judgments [61]; their design and analysis follow current methodological guidance for vignette data [62]. Each participant reads and evaluates all four scenarios of AI implementation (A–D), presented in a counterbalanced sequence. The within-subjects structure makes each respondent their own control, eliminating inter-individual variability from between-scenario comparisons and substantially increasing statistical power relative to a between-subjects design of the same size [63]. The presentation sequence is counterbalanced. The survey platform allocates participants at random, in equal proportions and independently of any participant characteristic, to one of the four sequences of a Williams (balanced Latin-square) design: A → B → C → D, B → D → A → C, C → A → D → B, and D → C → B → A. In this square, every scenario occupies every serial position exactly once, and every ordered pair of scenarios occurs exactly once, so that autonomy level is orthogonal both to serial position and to first-order carry-over, and an additive model containing a four-level autonomy effect and a four-level serial-position effect is fully identified. The theoretically motivated ascending sequence and its exact mirror image are retained as two of the four arms. A fixed ascending presentation would have mirrored the progressive continuum under investigation and given every participant an identical evaluation context, but it would have left order, carry-over, and fatigue effects inseparable from the autonomy gradient; because H1–H3 concern precisely that gradient, internal validity was given priority over uniformity of context. Counterbalancing also makes the embedded manipulation check diagnostic rather than merely descriptive: perceived AI control should track the described autonomy level within every sequence, whereas an anchoring or fatigue artifact would instead track serial position—a distinction that a monotonic manipulation-check profile obtained under a fixed order cannot draw. Presentation sequence is therefore retained as a between-subjects factor in all primary models, a second manipulation check (perceived technical sophistication) separates autonomy from technical complexity, and a per-scenario difficulty item indexes fatigue (Section 2.6, Section 2.7, Section 2.8, and Section 2.9.1). The study involves no medical, pharmacological, or surgical intervention. Reporting of the completed study will follow current recommendations for effect-size-based reporting [64] and, for the web-survey component, the CHERRIES checklist as operationalized in recent methodological guidance [65]. Publication of the protocol in advance of data collection is intended to reduce publication bias and analytic flexibility [66,67].

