
### 2.9. Statistical Analysis

#### 2.9.1. Primary Analyses

Each composite score (acceptability, trust, perceived risk) will be analyzed by a mixed repeated-measures ANOVA, with autonomy level (four scenarios) as the within-subjects factor and presentation sequence (four Williams sequences) as the between-subjects factor. The Greenhouse–Geisser correction will be applied when Mauchly’s test indicates a sphericity violation (Huynh–Feldt for ε between 0.75 and 1), and the multivariate approach (Pillai’s criterion) will be reported in parallel as a sphericity-robust check. H1 and H2 will be tested with within-subjects trend contrasts across the autonomy gradient. Because acceptance need not fall in a straight line, the complete set of orthogonal polynomial contrasts—linear, quadratic, and cubic—is pre-specified, and each is reported together with the proportion of the omnibus effect it accounts for. A purely linear profile leaves the quadratic and cubic components negligible, whereas a step between two adjacent levels appears as a large linear component accompanied by a substantial quadratic or cubic one. Because every monotone step is linear-dominant, the polynomial decomposition establishes departure from a straight line but cannot by itself locate the break; the break is identified only from the Holm-corrected adjacent-pair contrasts (A–B, B–C, C–D). A quadratic-dominant profile with a small linear component would instead indicate a non-monotone pattern, which the hypotheses do not predict and which would be reported as such. A non-monotonic or threshold pattern will be reported as such rather than summarized by the linear trend alone. Post hoc comparisons use dependent-samples *t*-tests for the six scenario pairs with Holm’s sequential correction, applied within each hypothesis-defined family of tests in line with current guidance on multiplicity control [74]. Effect sizes will be reported as partial η^2^ for omnibus tests and Cohen’s dz for pairwise comparisons, with 95% confidence intervals, following effect-size-centered reporting recommendations [64]. Assumption checks include graphical inspection of difference-score distributions; as a distributional robustness analysis, the Friedman test with Holm-corrected Wilcoxon signed-rank pairwise comparisons will be reported alongside each primary test—supplemented by ordinal (cumulative-link) models as sensitivity analyses for the Likert-based outcomes [71]—and the concordance of parametric and nonparametric conclusions stated explicitly. Order dependence is tested directly as the scenario × sequence interaction; a non-significant interaction, together with equivalence of the four sequence-specific profiles, supports pooling across sequences. Independently of that test, the autonomy effect is re-estimated from a linear mixed model with random intercepts per participant and additive fixed effects of autonomy level and serial position (1–4). The Williams square renders this model identified, so the estimate is adjusted for arbitrary—not merely linear—serial-position and fatigue effects, while first-order carry-over is balanced by the design rather than modeled; position-adjusted and unadjusted estimates are reported side by side, and any material divergence between them is treated as evidence of an order artifact and interpreted accordingly. Perceived difficulty (DIF1) and perceived technical sophistication (MAN2) are each added as time-varying covariates in further sensitivity models, addressing fatigue and the possibility that responses track the apparent complexity of the system rather than its autonomy. Finally, between-person heterogeneity in response profiles is examined by adding a random slope for the linear autonomy contrast and testing the improvement in fit by a likelihood-ratio test; a substantial random-slope variance indicates that an average trajectory conceals distinct response patterns and licenses the exploratory typology described in Section 2.9.2. Because a non-significant test is not evidence of absence, a smallest effect size of interest of *dz* = 0.20—the value detectable at the Bonferroni bound for the six pairwise contrasts at *N* = 300—is fixed in advance, and equivalence testing by two one-sided tests against that bound is reported alongside every null pairwise result, so that any claim that two adjacent scenarios do not differ rests on an equivalence test rather than on the absence of significance.

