## 3. Expected Results

Based on the algorithm-aversion and trust studies [19,37,38], we expect acceptability and trust to decline—and perceived risk to rise—across the autonomy gradient from Scenario A to Scenario D, with the largest drop anticipated at the transition to autonomous planning (Scenario D), where the surgeon’s corrective role is described as residual. Whether that decline is a gradient or a step is an open question that the design is equipped to address: a step would show as a substantial quadratic or cubic component alongside the linear one, and its location would be identified by the adjacent-pair contrasts, which we expect to place the largest single drop at C–D. Nor do we assume the pattern is homogeneous across participants; a substantial random-slope variance would itself be informative, indicating that an average trajectory conceals distinct groups of respondents rather than describing a shared response. The expectation of decline is, in any case, consistent with survey evidence that public comfort is conditional on physician supervision [24,25,31]. For responsibility attribution, we expect the surgeon to be assigned the dominant share in low-autonomy scenarios [41], with a progressive migration toward the AI developer—and possibly a diffusion of responsibility across actors, indexed by falling Herfindahl concentration—as autonomy increases [44,45]. We expect the manipulation check (perceived AI control) to order the scenarios from A to D within each of the four presentation sequences, validating the experimental gradient independently of serial position, and we expect no scenario × sequence interaction. Should one nevertheless appear, the position-adjusted mixed-model estimate becomes the primary basis for interpreting H1–H3, and the magnitude of the order effect will itself be reported as a finding about the stability of vignette-based autonomy judgments. Given the design’s sensitivity (power of 0.99 against small within-subjects effects at ρ = 0.50, and 0.95 at ρ = 0.30, for the target sample), a null result for a primary hypothesis would place a tight upper bound on the size of any autonomy effect rather than leaving the question open; the pre-specified equivalence tests of Section 2.9.1 make that bound explicit rather than infer absence from non-significance [70]. The moderation hypothesis (H4) is powered only for medium-small interactions and will be interpreted with corresponding caution. Results will inform the ordering of public concerns along the assistance-to-autonomy continuum and identify which implementation configurations are publicly acceptable entry points for surgical AI in Romania.

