Several limitations are accepted by design and will be declared in the results article. First, the sample is a self-selected online convenience sample: results describe Romanian adults active in digital environments—likely younger and more educated than the general population—and do not support national generalization; the sample structure will be reported against National Institute of Statistics reference data. Second, the vignettes are hypothetical, and the distance between a vignette judgment and a decision taken in a consulting room is not merely one of degree. Participants evaluate a scenario in which they are not injured, not in pain, not facing a scheduled operation, and not choosing between real surgeons. They bear no consequences for the judgment they record, receive no counseling, and cannot ask questions. Above all, they are not exposed to the most influential element of real surgical decision-making: a conversation with the clinician who would operate, whose endorsement and explanation are known to shift acceptance of AI-supported care substantially [27,28]. Stated acceptability under these conditions is best read as a measure of prior disposition toward a described scenario rather than as a prediction of consent behavior. The ordering of the scenarios is likely to be more robust than the absolute levels, which could be lower than those a counseled patient would report or higher if hypothetical risk is discounted. This is a standard limitation of vignette methodology [61,62], and the remedies lie outside the present design: replication among patients actually scheduled for facial reconstructive surgery, and ultimately observation of consent decisions where such systems are in use. Third, presentation sequence is counterbalanced but not thereby rendered irrelevant. The Williams square balances serial position and first-order carry-over, so that the autonomy effect is estimable free of both, but no four-sequence design balances higher-order carry-over—a participant’s evaluation of the third scenario being shaped jointly by the first two—and contrast effects that depend on which scenario was seen immediately before therefore remain possible. The scenario × sequence interaction, the position-adjusted model, and the difficulty covariate bound the magnitude of what remains; they do not remove it, and a large residual would warrant a between-subjects replication in which each participant evaluates a single scenario. Fourth, demand and contrast effects are inherent to within-subjects designs: seeing all scenarios, participants may infer the study objective and exaggerate differentiation between scenarios; comparisons remain internally valid, but absolute difference magnitudes warrant caution. Fifth, all measures share a common method and a single measurement occasion, in a rapidly evolving attitude domain [38]. Sixth, the survey platform does not record completion time, so quality control relies on embedded checks rather than temporal filters [69]. Seventh, the demographic and familiarity subgroups formed within a convenience sample of 300 will differ substantially in size, and several will be small; the minimum-cell rule of Section 2.9.2, and the requirement that subgroup differences be inferred only from formal interaction terms, are intended to forestall the familiar error of asserting a difference from a significant effect in the larger subgroup together with a non-significant one in the smaller. None of these limitations is unusual for online vignette experiments, and declaring them in advance is intended to keep the eventual findings interpretable at their proper scope.

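### First-order carry-over is balanced but not orthogonal to autonomy level: with no term for it, a quarter of any carry-over difference enters every autonomy contrast

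*Protocol article*

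**What the plan says.** Section 2.1 allocates participants "in equal proportions and independently of any participant characteristic" to the sequences ABCD, BDAC, CADB and DCBA, and states that "every ordered pair of scenarios occurs exactly once, so that autonomy level is orthogonal both to serial position and to first-order carry-over". The Abstract makes the same claim.

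Section 2.9.1 draws the consequence for the analysis: "first-order carry-over is balanced by the design rather than modeled". The linear mixed model there has fixed effects for autonomy level and serial position and a random participant intercept. The mixed ANOVA has scenario, sequence and their interaction.

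Section 3 says that if the scenario × sequence interaction is non-null, "the position-adjusted mixed-model estimate becomes the primary basis for interpreting H1–H3".

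Section 4 presents separation from first-order carry-over as the fourth principal contribution, and the limitations say: "The Williams square balances serial position and first-order carry-over, so that the autonomy effect is estimable free of both". The same limitation concedes that contrast effects from the scenario read immediately before may remain, but attributes them to higher-order carry-over.

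**The concern.** Balance and orthogonality are different properties. A Williams square balances first-order carry-over, in that each scenario follows each other scenario equally often. It does not make scenario and carry-over orthogonal, because a scenario never follows itself. A model without a carry-over term then gives scenario contrasts that are biased whenever scenarios differ in what they carry forward.

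Carry-over is one of the two threats that Section 4 calls the main danger to internal validity in graded-vignette designs. If a reader's rating moves away from the preceding vignette, the autonomy gradient is inflated. If it moves towards it, the gradient is shrunk. The effect sizes, the location of a break from adjacent-pair contrasts, and the equivalence tests all depend on contrasts that carry this bias. The effect of the immediately preceding scenario is by definition first-order carry-over, so the limitations passage also contradicts itself.

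**Working it through.** **Inputs.** Sequences and equal allocation from Section 2.1. N = 300, ρ = 0.50, two-sided α = 0.05 and power 0.80 from Section 2.5. Equivalence bound dz = 0.20 from Section 2.9.1. The size of carry-over is not in the document and is assumed over a range.

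**1. The plan's own figures.** With noncentrality f²·N·4/(1 − ρ) and df 3 and 3(300 − 4) = 888, the minimum detectable f is 0.068, stated as 0.07. For the 9-df interaction it is 0.081, stated as 0.08, and power at f = 0.10 is 0.95, as stated. The power section reproduces.

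**2. The square.** Each scenario holds each position once. All 12 ordered pairs of different scenarios occur once, and no self-pair occurs. The scenario-by-predecessor counts are 0 on the diagonal and 1 elsewhere. After sequence and position are removed, the cross-products are −0.75 on the diagonal and +0.25 off it. Orthogonality would need zeros throughout.

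**3. The bias.** Let τ be the autonomy effect and λ the additive carry-over. Scenario i comes first once and follows each of the other three once, so apart from constants

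- mean of i = τi + (Σλ − λi)/4
- contrast i − k = (τi − τk) − (λi − λk)/4

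Least squares on the 16 cells confirms this. With carry-over of 1 from D only and no autonomy effect, D–A is −0.25 both with and without position adjustment. A–B and B–C are unaffected, and C–D shifts by 0.25. Equal carry-over from all four scenarios gives no bias.

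**4. Size.** At ρ = 0.50 the paired difference has SD √(2(1 − 0.50)) = 1 in outcome SD units. For carry-over linear in autonomy level, no true autonomy effect and N = 300:

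| D–A carry-over difference (SD) | False D–A dz (absolute) | Uncorrected rejection rate for D–A | Power of scenario × sequence test |
|---|---|---|---|
| 0.2 | 0.05 | 0.14 | 0.69 |
| 0.4 | 0.10 | 0.41 | near 1 |
| 0.8 | 0.20 | 0.93 | near 1 |

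The nominal rejection rate is 0.05. At ρ = 0.30 the three rates are 0.11, 0.31 and 0.83.

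If carry-over is instead a fraction c of each scenario's own effect, the gradient is multiplied by 1 − c/4, with c negative for contrast. For a true D–A effect of −1.00:

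- c = 0.5 gives −1.00 × (1 − 0.125) = −0.875
- c = −0.5 gives −1.00 × (1 + 0.125) = −1.125

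The model with a carry-over term returns −1.00 in both cases.

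**5. Cost of the term.** With sequence, position, scenario and preceding scenario fitted, the design has full rank (13 parameters, 16 cells). The variance of a pairwise contrast rises from 0.50 to 0.55 per replicate of the square, a ratio of 1.10. The standard error rises by √1.10 = 1.049. The minimum detectable f becomes 0.0675 × 1.049 = 0.071.

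**The case against.** The algebra is not in dispute. The case for leaving the plan alone has four parts.

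- **Direction survives.** If carry-over is proportional to each scenario's own effect, the gradient is rescaled but keeps its sign, order and shape, and a true null stays null. H1–H3 fix direction only. This stands for that form of carry-over. The false rejections in the table need carry-over without an autonomy effect, and the document gives no size for either.
- **The plan already detects it.** The scenario × sequence interaction contains the carry-over component and would usually flag a difference of 0.4 SD. This stands as detection. The planned response does not cure the problem, because Section 3 then moves to a model that has no carry-over term and the same bias. The comparison of adjusted with unadjusted estimates cannot show it either.
- **The limitations urge caution.** Section 4 warns that differentiation may be exaggerated and that absolute differences need care. That softens the practical consequence. It does not correct the statement that the effect is estimable free of carry-over, which is true of the design only if the term is fitted.
- **The remedy is exact only for additive carry-over.** This stands. If the rating shifts by half the difference between the current and the preceding scenario, a true D–A of −1.00 becomes −1.50 in the planned models and −1.375 with the carry-over term. Only 0.125 of the 0.50 distortion is removed.

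**Conclusion.** The concern holds. As planned, both the mixed ANOVA and the position-adjusted model carry a bias of −(λi − λk)/4 in every autonomy contrast, so the claims of orthogonality and of freedom from first-order carry-over are wrong for the planned analysis. The quarter follows from the stated sequences under equal allocation and additive carry-over. Its practical size depends on an unknown: a D–A carry-over difference of 0.2 to 0.8 SD gives a shift of 0.05 to 0.20 SD, and at ρ = 0.50 the upper end equals the equivalence bound. A large directional effect for H1 or H2 would survive proportional carry-over. The estimated magnitudes, the location of a break and the equivalence conclusions are more exposed. Section 2.12 reports that data collection has not started and that pre-registration is still to come, so this can be corrected now.

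**What to change.** - **Model.** Add a fixed effect for the immediately preceding scenario (3 df, set to none at position 1) to the mixed models for acceptability, trust and perceived risk. For H3, cross it with actor, because the test is the scenario × actor interaction and a term common to all actors would not change it.
- **Reporting.** Give the carry-over-adjusted contrasts and the 3-df carry-over test beside the ANOVA and the position-adjusted results.
- **Fallback.** In Section 3, make the model with both position and preceding scenario the basis for interpretation when the interaction is non-null.
- **Wording.** In the Abstract, Sections 2.1 and 2.9.1, and both places in Section 4, say that the design is balanced for first-order carry-over, which is estimated in the model under an additive assumption. In the limitations, name the effect of the immediately preceding scenario as first-order, and say that contrast depending on the pair of scenarios is only partly removed.

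The cost is one model term, crossed with actor for H3, and these text changes. Standard errors of the contrasts in that model rise by about 5%, and the minimum detectable effect for the composites still rounds to f = 0.07. The planned ANOVA can stay as it is.

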
### 2.2. Experimental Vignettes

The four vignettes describe distinct configurations of AI involvement in facial reconstructive surgical planning, varying both the AI’s task (imaging analysis, decision support, outcome simulation, autonomous planning) and the surgeon’s level of supervision (Table 1). Each configuration corresponds to a capability documented in the current literature: anatomical structure analysis from CT [6,8], algorithmic generation of candidate surgical plans [9], three-dimensional simulation of postoperative facial appearance [12,13], and highly autonomous planning of the kind anticipated by surgical-autonomy frameworks [14,15]. All vignettes open with an identical premise (the respondent needs facial reconstructive surgery following an injury) and are written in parallel second-person wording of comparable length and reading difficulty, so that scenario content—not framing—drives differences in responses. Because the four configurations differ in what the AI does as well as in how much the surgeon decides, a perceived difference between them could in principle reflect technical sophistication rather than autonomy. Three features are intended to keep the two apart. First, every vignette closes by stating explicitly how the final surgical plan is reached and by whom. In Scenarios A–C, a single clause of parallel construction names the surgeon as the decision-maker (making all decisions, choosing among the proposed options, or deciding the final plan after reviewing the simulations); in Scenario D, the closing sentences state that the surgeon reviews the AI’s plan but rarely modifies it. What varies is therefore the decisional locus, not the computational task. Each comprehension check is built on that same feature: the decision-maker in Scenarios A and B; the role of the system in Scenario C (whose decisional clause is functionally equivalent to Scenario B’s, so that the role is what distinguishes the two); and the origin of the plan actually followed in Scenario D. Second, the vignettes are matched on the quantity of technical detail supplied—one sentence describing the system’s input and output in each case—so that described sophistication does not rise in step with autonomy. Scenario C specifies a generative three-dimensional simulation, computationally the most elaborate output in the set, yet leaves the decision entirely with the surgeon; Scenario D describes a comparatively conventional optimization whose distinguishing feature is decisional rather than technical. Third, two manipulation checks follow every scenario: MAN1, perceived control of the AI over the final decision, and MAN2, perceived technical sophistication of the system. The manipulation is treated as valid only if MAN1 orders the scenarios as intended; MAN2 verifies that sophistication does not itself increase monotonically with autonomy and enters a pre-specified sensitivity analysis as a covariate, so that the autonomy effect can be estimated with perceived sophistication held constant (Section 2.9.1). The full vignette texts are provided in Appendix A.
